### Statistical analyses

#### Step 1 routine dissemination: fact sheet intervention

Descriptive statistics only will be used to describe the reach of the factsheet; and whether participants in Step 2 and Step 3 recall receiving the factsheet.

#### Step 2 targeted dissemination: booklet intervention

Using oneway analyses of variance (ANOVA), the relationship between demographic data (e.g. gender, age categories, ethnicity, socioeconomic level, help-seeking behaviour categories) and baseline outcome measures will be explored.

The impact of the booklet intervention will be examined using analysis of covariance (ANCOVA) to compare changes in mean scores from baseline to three-month follow-up on the outcome measures for all participants in Step 2 (n ≈ 353). To test for sustained change, a second analysis of the Step 2 participants will use a repeated measures mixed model to compare mean scores on outcome measures at baseline, three and six month follow-up for the participants who did *not* move into Step 3 (the Information Support Group Intervention phase). Further analyses will adjust for baseline characteristics to control for any confounding effects.

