### Study aim and hypotheses

This study aims to improve the resilience and wellbeing of families caring for a child living with chronic illness. Specifically, the objectives of the study are to: 1) improve the capacity of health services to provide family resilience information and strategies to families; 2) determine if the CHiRP resources are acceptable to parents; 3) increase parents knowledge and confidence to implement strategies to improve their family resilience; 4) promote parental help seeking behaviours and 5) improve the resilience and psychological wellbeing of families by providing a stepped care intervention to parents that increases in intensity according to the family’s situation. It is hypothesised that a significant positive improvement in outcome measures of constructs indicating family resilience (parental wellbeing, family functioning, family beliefs, and perceived social support) will be observed between baseline and follow up assessments as a result of receiving a family resilience self-directed booklet. Furthermore, for parents who are experiencing psychological distress, it is hypothesised that participation in a parent information support group (in addition to receiving the booklet) will result in greater improvement on the same outcome measures. It is further anticipated that participants will report that the intervention content and delivery style is acceptable.

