## Methods/Design

### Study design and setting

The setting is a paediatric hospital in regional New South Wales that provides healthcare services to approximately 16,675 children per year who reside in the Newcastle, Hunter and New England regions (Australia). The intervention uses a stepped care design, such that increasing levels of intervention support are provided to families living with childhood chronic illness based on the level of parental distress. Step one involves the routine dissemination of a Family Resilience and Wellbeing Fact Sheet using single group assignment. Step two involves the targeted dissemination of a parent-focussed Family Resilience and Wellbeing information and activity booklet and will employ a repeated measures pre-post design. Step three involves the active participation of parents in a Family Resilience and Wellbeing Information Support Group and will employ a randomised waitlist control design. The dissemination strategy and research design for each step of the intervention is outlined in Figure 1.

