### Sample size

In Step 1, it is expected that the Fact Sheet will be provided to 1050 parents of children discharged from paediatric hospital services based on an estimate of inpatient numbers over a 12-month period in 2011. There will be no direct data collection from this group.

A sample size calculation was conducted to guide recruitment for Step 2, the booklet intervention. Using mean estimates based on normative scores (Andrews & Slade 2001; Kabacoff et al. 1990; Sherbourne & Stewart 1991; Sixbey 2008) and a hypothesised effect size of 0.2 as a result of receiving the family resilience and wellbeing booklet, a minimum sample of 98 participants at the three-month follow up assessment will have sufficient power (0.8) to detect a significant difference between mean scores (using alpha 0.05) in a one-sample comparison of baseline and three month follow-up data. A larger sample size will be recruited, however, to allow for attrition and sufficient numbers of participants eligible for Step 3.

In Step 3, the Parent Information Support Group intervention, using a randomised waitlist control design, the sample size will be divided randomly and equally between the group condition and the waitlist control condition. A sample size calculation used mean estimates based on a sample of Australian patients diagnosed with a mental disorder (Kohn et al. 2012) using the K10 and normative scores for the other outcome measures of interest. Effect sizes of 0.5 and 0.3 were hypothesised as a result of receiving the booklet intervention and participating in the information support group intervention or being in the control group, respectively. A sample size of approximately 120 (60 per group) participants at the three month follow up assessment will allow detection of a significant difference between mean scores using an alpha level of 0.05 in a two-sample comparison of the group condition and control condition on the outcome measures, with a power of at least 0.8.

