CHiRP will employ a stepped care design to meet the demands of scientific rigour as well as conform to the pragmatic considerations involved in implementing research in a busy paediatric hospital setting. The dissemination of the Fact Sheet in Step 1, as part of routine paediatric discharge procedures, maximises the opportunity for families of hospitalised children (regardless of reason for admission) to receive brief, standardised information regarding ways to promote family resilience. The use of a single group pre-post design in Step 2, while potentially limiting the generalizability of outcomes for the booklet intervention, corresponds to the practicalities involved in implementing mental health promotion practices in the busy outpatient clinic environment (Merkel & Wright 2012). The use of a randomised waitlist control group in Step 3 ensures that the impact of the Information Support group can be rigorously evaluated, while allowing all consenting parents who are experiencing psychological distress to receive the highest level of intensity of the CHiRP intervention.

CHiRP meets an identified need for mental health promotion and prevention interventions that enhance family resilience and wellbeing in families of children with chronic illness who are more vulnerable to mental health issues. Through provision of the Family Resilience Fact Sheet and the Strong Parents, Resilient Families workbook, this study will provide information and strategies in a format that families can access and work through independently, without relying on intensive mental health or medical professional delivery. These family interventions are designed to empower parents to help the whole family cope better by learning new strategies and interacting with each other (Marsac et al. 2012). Further, through provision of the Information Support Group this study will provide additional support to parents reporting the highest levels of distress. If effective, CHiRP will increase the capacity of health services to provide standardised family resilience information and strategies to families living with a child with chronic illness.

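### The main Step 2 test is a single-group ANCOVA with no stated group or time factor, and a design without a control cannot attribute change to the booklet

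*Protocol article*

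**What the plan says.** Under Study design and setting, Step 2 "will employ a repeated measures pre-post design"; the Discussion describes it as having a single group. Under Statistical analyses, Step 2, the main analysis reads: "The impact of the booklet intervention will be examined using analysis of covariance (ANCOVA) to compare changes in mean scores from baseline to three-month follow-up". It covers all Step 2 participants, given as about 353. No factor or covariate is named for it.

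Two further Step 2 analyses follow. In the first, "a second analysis of the Step 2 participants will use a repeated measures mixed model to compare mean scores on outcome measures at baseline, three" (the list goes on to the six-month assessment); it is restricted to participants who did not move into Step 3. The second is described as: "Further analyses will adjust for baseline characteristics to control for any confounding effects".

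The Sample size section gives a minimum of 98 at three months, for an effect size of 0.2, alpha 0.05 and power 0.8, "in a one-sample comparison of baseline and three month follow-up data".

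On interpretation, Study aim and hypotheses expects improvement "as a result of receiving a family resilience self-directed booklet". The Discussion describes the single-group design as suited to a busy clinic, "while potentially limiting the generalizability of outcomes for the booklet intervention". It reserves rigorous evaluation for the randomised Step 3.

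**The concern.** ANCOVA ordinarily compares adjusted means between groups, and Step 2 has only one group. As written, the reader cannot tell which model term would answer the question of whether mean scores changed by three months. The terms that such a model usually reports do not answer it. The test that was powered is a different one.

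The first hypothesis rests on this analysis, and that hypothesis is causal. Without a concurrent control, a correctly tested change still could not be separated from other things that happen between two questionnaires. Limited generalisability is a question of external validity. The limitation that matters here is internal validity.

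**Working it through.** **1. The plan's own figure.** Inputs from Sample size: d = 0.2, alpha 0.05, power 0.8, one sample.

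- Two-sided: n = ((1.960 + 0.842)/0.2)² = 196.2, so 197 (199 with the noncentral t).
- One-sided: n = 154.6, so 155 (156 with the noncentral t).
- The stated 98 does not follow from these inputs alone. If 0.2 is in baseline-SD units and the pre-post correlation is ρ, the two-sided n = 2(1 − ρ) × 196.2. At ρ = 0.75 this is 98.1. At ρ = 0.5, 0.6, 0.7 and 0.8 it is 197, 157, 118 and 79.

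The article does not state ρ, so 98 is neither confirmed nor shown to be wrong. The present point does not depend on it.

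**2. What a one-group ANCOVA tests.** Fit change = a + b × baseline + error. Assume (not in the document) unit SDs, ρ = 0.75, no true change, n = 353 and a scale mean 5 SD above zero.

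- Slope: b = ρ − 1 = −0.25. Residual SD = √(1 − 0.75²) = 0.661. SE = 0.661/√353 = 0.035. Ratio about −7.1.
- Uncentred intercept: 0.25 × 5 = 1.25. SE = 0.0352 × √(1 + 5²) = 0.179. Ratio about 7.0.
- Intercept with baseline centred at its sample mean: this is the mean change. Its SE uses the residual SD of 0.661, whereas the SD of change is √(2 × 0.25) = 0.707. The effective critical value is 1.96 × 0.661/0.707 = 1.83, a two-sided error of about 0.067.

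A simulation of 4,000 trials with zero true change agrees:

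| Test | Rejections |
|---|---|
| Baseline slope | 100% |
| Uncentred intercept | 100% |
| Centred intercept | 6.8% |
| Paired t-test | 5.2% |

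The first two do not test mean change. The third does, slightly liberally. The paired test does so at its nominal level.

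**3. Passages side by side.** Sample size powers a one-sample comparison of baseline with three months; Statistical analyses, Step 2 names an ANCOVA. For Step 3 the same label is used with an explicit factor, Group versus Waitlist, and the later Step 3 analysis is expressly said to have no allocation variable. Step 2 has no equivalent statement.

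**4. Whether the mixed model can stand in.** It leaves out participants who moved into Step 3, for which eligibility was a three-month K10 above 15. On the planning figures that is about 120 of 353 (34%), leaving about 233. The exclusion depends on the outcome at the time point being tested. Removing parents with high three-month scores tends to pull the remaining K10 change towards improvement, so this model does not estimate change in all participants.

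**5. Rival explanations.** Under Data collection procedures, baseline is completed on paper or online, while follow-up may be by telephone with a member of the study team. Baseline runs September 2013 to March 2014 and three-month follow-up January to June 2014. Baseline is tied to a coming clinic visit, whereas follow-up is timed from baseline. Time trend, retesting and survey mode can all move self-reported scores. Fixed baseline characteristics do not change between the two assessments, so adjusting for them does not remove these effects.

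**6. Illustration of size.** Assume a drift of 0.2 SD of change unrelated to the booklet. With n = 353 the noncentrality is 0.2 × √353 = 3.76, the critical value is 1.97, and the probability of significance is about Φ(1.79) = 0.96. With n = 98 it is 0.2 × √98 = 1.98, and the probability is about 0.50.

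**The case against.** The strongest reply is that the text already implies a within-person contrast. The design is called repeated measures, the sample size is for one sample, and the ANCOVA is said to compare changes from baseline. A repeated-measures ANCOVA with time as a within-subject factor, or a change-score model with centred covariates, would fit that description and would test mean change. Coding and centring are details that a condensed article may leave to a fuller plan. This stands in part: it rules out the inference that nothing called ANCOVA could test change here. But the article names a method, and that method in its conventional form does not fit the design or match the powered test.

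A reader might also infer that the two time points would be analysed as independent, with an inflated variance. Nothing in the article proposes that, and with positive correlation it would make the test conservative.

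A reader might infer that baseline adjustment is useless. That goes too far: covariates related to dropout can alter the estimated time effect, and covariates may improve precision. It is the stated purpose, control of confounding, that adjustment does not achieve for time, retest or mode effects.

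On attribution, the Abstract puts the overall hypothesis in terms of association, and the Discussion is open about the single group. Regression to the mean is also a weaker rival here than in Step 3, because Step 2 does not select on distress. These points soften the concern but do not cure it, since the hypothesis under Study aim and hypotheses is causal and internal validity is not mentioned.

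**Conclusion.** The point holds in two parts. First, the main Step 2 analysis is named in a form that conventionally does not test mean change and differs from the comparison that was powered. The only explicit repeated-measures model for Step 2 covers a subset whose exclusions depend on the three-month outcome. Second, the wording attributes change to the booklet in a design with no concurrent control, and the limitation conceded is not the main one.

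The first part rests on the text alone; the simulation only illustrates it, under an assumed correlation of 0.75. The 0.96 is also an illustration. It assumes a drift of 0.2 SD of change and three-month data from all 353, and falls to about 0.50 with 98. The article gives no estimate of drift, so 0.96 should not be read as the plan's false-positive rate.

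**What to change.** Replace the Step 2 ANCOVA with a paired test of change, or with a mixed model that has time as a fixed effect and participant as a random effect. Apply it to all Step 2 participants at baseline and three months, and report mean change with its CI. The mixed model equals the paired test only when data are complete, so state which is primary. Keep the three-time-point model as a secondary analysis of those who did not enter Step 3, labelled as such.

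In Study aim and hypotheses and in the Step 2 analysis, replace the wording on result and impact with change following receipt of the booklet. In the Discussion, name the lack of a control, and hence internal validity, as the limitation. Reserve effectiveness claims for the randomised Step 3 comparison, which concerns the group added to the booklet and not the booklet itself. Describe baseline adjustment as serving precision or dropout, not confounding.

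The cost is confined to the analysis specification and wording, with no new data or procedures. The downside is a more modest claim for the booklet.

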#### Step 3 active dissemination: parent information support group intervention

Participants who report psychological distress at the 3-month follow up of Step 2 will be considered eligible to participate in Step 3 of the intervention. Psychological distress will be defined according to cut off scores on the Kessler Psychological Distress Scale (K10) (Kessler et al. 2003). There is some evidence that support groups are of optimal benefit for this portion of the target population (Turner et al. 2001). All parents reporting a K10 score above 15 (Slade et al. 2011) will be eligible for the group. Eligible parents will be contacted by phone by a member of the CHiRP research team and invited to attend an Information Support Group. Participants who agree to attend the Information Support Group will be randomly allocated to the group or waitlist condition using standard statistical computer software. Researchers will not be blinded to group assignment. Participants will be notified by phone and letter of the date of group commencement.

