#### Step 3 active dissemination: parent information support group intervention

The data from the three-month follow-up assessment for Step 2 will constitute the baseline (or pre-group) data for Step 3. Participants in Step 3 will also complete an additional questionnaire at the first group session regarding their expectations of the group and what mental health support they might already be receiving. Medical records for the child of parents in Step 3 will be reviewed to record any hospital-based nursing or allied health staff involvement with the family.

On completion of the Information Support group, participants will be provided with the follow up questionnaire as part of the last group session. Follow up assessment of the group intervention will occur between April – September 2014. Participants in the waitlist control group will be completing the 6-month follow up assessment from baseline in Step 2 of the study at this time. This will provide the control comparison data to assess the additional impact of the group intervention, compared to receiving the booklet alone. The waitlist control group will then proceed to participate in the group intervention. All participants in Step 3 will be scheduled to complete a final follow up (single-group) assessment six months after they attended the group. This will provide repeated measures pre-post data regarding the longer-term efficacy of the group intervention. Participants will receive a prompt letter regarding six month follow up and approximately two weeks later a phone call, giving them the option to complete the questionnaire over the phone, online or receive a hard copy in the mail. Six-month follow up of participants in Step 3 is anticipated to occur between October 2014 – March 2015.

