#### Step 3 active dissemination: information support group intervention

Initial analyses will use demographic data to compare the characteristics of participants who agree to participate in Step 3 compared to those who decline to participate in this step of the project (despite meeting eligibility criteria, i.e. K10 > 15). Differences in responses according to demographic variables on the construct measures of interest (K10, FAD, family belief systems and MOSSSS) will also be analysed using oneway ANOVAs.

To examine the additional impact of the information support group intervention, relative to the wait-list control group (who will have only received the booklet intervention), an analysis of covariance will examine changes in mean scores on the outcome measures from baseline to post-intervention follow-up according to Group (n ≈ 60) versus Waitlist (n ≈ 60) allocation. To account for participant deviations from the protocol (such as dropout or failure to sufficiently participate in the group intervention), two analyses will be conducted. Data will be analysed using the intention-to-treat principle, which will assume all participants randomised to the intervention or waitlist group completed the study as per the research design and a per-protocol analysis will include only those participants who participate in a minimum of two-thirds of the intervention (Porta et al. 2007). Following post-intervention follow-up data collection, the waitlist group will complete the information support group intervention, and complete the post-intervention follow up. All group-based intervention participants will complete a six-month follow-up assessment. Thus, to test for sustained change, a second analysis will compare mean scores at baseline, post-intervention and six-month follow up on the same outcome measures for all participants in Step 3 of the intervention (n ≈ 120). There will be no treatment allocation variable in this second analysis. Further analyses will adjust for baseline characteristics to control for any confounding effects.

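### The Step 2 sustained-change model is fitted to a set selected partly on the 3-month K10, which distorts its 3-month mean and its 3-to-6-month trajectory

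*Protocol article*

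**What the plan says.** The protocol article plans two analyses of the booklet (Statistical analyses, Step 2). The first covers baseline to 3 months "for all participants in Step 2 (n ≈ 353"). The second is a repeated measures mixed model for sustained change, restricted to a subset: it compares "mean scores on outcome measures at baseline, three and six month follow-up for the participants who did *not* move into Step 3". Further analyses adjust for baseline characteristics.

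Who moves is set out under Participants and recruitment, Step 3. On timing: "Participants who report psychological distress at the 3-month follow up of Step 2 will be considered eligible to participate in Step 3". On the threshold: "All parents reporting a K10 score above 15" qualify. Consent is also needed: "Participants who agree to attend the Information Support Group will be randomly allocated to the group or waitlist condition". The K10 is itself one of the outcome measures.

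Under Data collection procedures, Step 3, the waitlist arm completes the Step 2 6-month assessment before it attends the group. The article says of these data: "This will provide the control comparison data to assess the additional impact of the group intervention, compared to receiving the booklet alone". They are therefore booklet-only observations.

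**The concern.** Leaving out parents who moved into Step 3 removes people because their K10 was high at 3 months. Some of those scores were high by chance at that visit. The parents who remain have 3-month scores that are on average too low relative to their own baseline and 6-month scores. Even if the booklet does nothing, the fitted means will fall from baseline to 3 months and rise again by 6 months.

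The false gain lies in the direction of the hypothesis, and the false loss looks like a fading effect, in the one analysis intended to show whether change lasts. Adjusting for baseline characteristics does not remove this, because the selection acts on the 3-month score.

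The restriction also narrows the population. The hypothesis concerns parents who receive the booklet, but the planned set omits about a third of them, all distressed at 3 months. It also leaves out the waitlist arm's 6-month scores, which come from a random half of those who moved and reflect the booklet alone.

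**Working it through.** **Inputs from the article.** Step 2 has about 353 participants. The sustained-change analysis of Step 3 is "for all participants in Step 3 of the intervention (n ≈ 120"). The share removed is q = 120/353 = 0.340, leaving 353 − 120 = 233. The hypothesised Step 2 effect size is 0.2, with a minimum of 98 participants, power 0.8 and alpha 0.05 in a one-sample comparison (Sample size).

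**Not in the article, so assumed.** The between-visit K10 correlation r, the share of parents above the cut-off, and the uptake among them.

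**The plan's own figure.** n = ((1.96 + 0.842) × SD_diff / 0.2)², two-sided.
- SD_diff = 1 gives 196.2, so 98 does not follow from the stated inputs alone.
- SD_diff = √(2(1 − r)) with r = 0.75 gives 98.1, which matches.

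The article does not state r, so 98 is not called wrong. It suggests r = 0.75 as one plausible value.

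**False 3-month change, every eligible parent joining.** Take normal scores in SD units with no true change and the top 34% at 3 months removed. The cut is c = 0.413, and the remaining parents average −φ(c)/Φ(c) = −0.366/0.660 = −0.555 at 3 months and −0.555r at baseline. The false improvement is (1 − r) × 0.555:

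| r | False change (SD) | Chance of a significant result, n = 233, no true effect |
|---|---|---|
| 0.5 | 0.28 | 0.99 |
| 0.6 | 0.22 | 0.98 |
| 0.7 | 0.17 | 0.92 |
| 0.75 | 0.14 | 0.87 |
| 0.8 | 0.11 | 0.80 |

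The last column is for a two-sided 5% test of the 3-month change. Simulation with three equally correlated visits agreed. With right-skewed scores the false change was 0.25 to 0.10 SD (observed correlations 0.42 to 0.75).

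**Some eligible parents decline.** If a share e is eligible and uptake is q/e, unrelated to the score, the 3-month mean of those left is −q × (φ(c_e)/e)/(1 − q), where c_e cuts off the top share e.
- e = 0.5, uptake 68%: −0.340 × 0.798/0.660 = −0.411. The false change is 0.21 SD (r = 0.5), 0.10 (0.75) and 0.08 (0.8).
- e = 0.7, uptake 49%: −0.256. The false change is 0.13 SD (r = 0.5), 0.06 (0.75) and 0.05 (0.8). The chance of a false significant result is still 24% to 50%.

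**Baseline to 6 months.** The false improvement is (r between 3 and 6 months − r between baseline and 3 months) × 0.555. It is zero when the two are equal and ±0.1 × 0.555 = ±0.06 SD when they differ by 0.1. The false 3-month gain is therefore followed by a false loss of about the same size.

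**Other scales.** The false 3-month change is (concurrent correlation with the K10 − cross-lag correlation) × 0.555. Assumed pairs of 0.3 and 0.2, 0.5 and 0.35, and 0.5 and 0.4 give 0.06, 0.08 and 0.06 SD with every eligible parent joining.

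**After the repair.** All 353 baseline and 3-month scores were kept, and every Step 3 participant's 6-month score was treated as missing under likelihood estimation. The false change was then 0.00 SD at 3 months and within 0.01 SD of zero at 6 months, for r = 0.5, 0.6 and 0.75. This run did not use the waitlist scores, which add information.

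**The case against.** The exclusion has a purpose. Half of those who move receive the group before the 6-month time point, and their later scores no longer describe the booklet alone. That stands, but it justifies setting aside only the immediate-group arm's 6-month scores. It does not justify dropping anyone's baseline and 3-month scores, or the waitlist arm.

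Four stronger readings are tempting, and the documents do not support them.
- A reader might infer that the false change equals the hypothesised 0.2. That needs r near 0.64 with full uptake, or a lower r with some decliners. At r = 0.75, the value that reproduces 98, it is at most 0.14 SD.
- A reader might take the set to be purely low scorers. Distressed parents who decline stay in it, and the article expects decliners and plans to compare them with those who agree. They dilute the bias.
- A reader might conclude that the booklet's 3-month result is compromised. The main 3-month comparison uses all participants, so an unselected estimate of that contrast will exist.
- A reader might infer, because the first analysis is called an ANCOVA in a single group, that pairing is lost. The article does not name the covariate or say that the two visits are treated as independent groups, and its sample size rests on a one-sample comparison. No point is made of this here.

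**Conclusion.** The concern holds for the sustained-change model only. Its analysis set is selected partly on the 3-month K10, and the article neither mentions nor corrects for this. The K10 mean at 3 months and the 3-to-6-month trajectory are biased. The false change is 0.11 to 0.28 SD with full uptake (0.14 SD at r = 0.75) and falls to about 0.05 SD when many decline. This may be a substantial part of the 0.2 effect, depending on a correlation and an uptake that the article does not give. The bias is probably smaller for the family functioning, social support and family beliefs scales.

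The baseline-to-6-month contrast has little bias if adjacent correlations are similar, but it applies to a less distressed subset than all booklet recipients. All sizes assume no true change, 120 of 353 moving, and declining unrelated to the score among those eligible.

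**What to change.** Keep the first Step 2 analysis on all participants. Reword the second so that the mixed model is fitted by likelihood to all Step 2 participants (n ≈ 353), with:
- all baseline and 3-month scores;
- all 6-month scores obtained after the booklet alone, from parents who did not enter Step 3 and from the waitlist arm;
- only the immediate-group arm's 6-month scores set to missing.

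Among parents who agreed, randomisation decides that missingness, and the 3-month K10 that led to eligibility is observed. No weighting of the waitlist arm is needed, provided that agreeing to attend tells nothing more about the 6-month score once earlier scores are in the model. The waitlist data allow that to be checked. For the other scales, the 3-month K10 should be carried in the model as an additional response, since it drives the selection.

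The cost is a change of analysis wording. All the data are already scheduled for collection.
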